### 2.1. Ethical Statement

All the procedures performed in the study will be run following the ethical standards of the institutional and/or national research committee and in compliance with the Declaration of Helsinki and its later amendments or comparable ethical standards.

The study was approved by the Ethical Committee of IRCCS, Istituto Auxologico Italiano, (ID: 03C214) on 17 May 2022. Important protocol amendments will be communicated promptly to investigators, ethics committees, and regulatory authorities as required.

### 2.2. Study Population

Participants will be recruited in the first week of admission to the 1-month nutritional rehabilitation program in the three specialized centers. The inclusion criteria will be as follows: (1) receiving a diagnosis of AN according to the DSM-5 criteria [1]; (2) being over 18 years old; (3) having fluent Italian; and (4) signing the informed consent to participate in the study. Participants will be excluded from the study if they present with (1) specific learning disabilities (SLDs) or intellectual disability, (2) psychosis, (3) head injury, (4) history of psychotropic substance use, or (5) other clinical sensorial impairment (visual or hearing one) preventing them from following the intervention. Participants receiving pharmacological treatment will not be excluded from the study.

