### 2.4. Randomization and Blinding

Randomization will be stratified by center and performed using the permuted block technique within each site by a researcher independent of the study. Due to the nature of the intervention, the group allocation cannot be concealed from the participants or the provider of the intervention. Participants will be assigned to one of two conditions within the first week from the baseline assessment (Figure 1).

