The World Health Organization Quality of Life (WHOQOL-BREF) [70]: A self-assessment questionnaire consisting of 26 items rated on a 5-point Likert scale and grouped into four dimensions: physical health (i.e., mobility, daily activities, functional capacity, energy, pain, and sleep), psychological health (i.e., self-image, negative thoughts, positive attitudes, self-esteem, mindset, learning ability, memory concentration, religion, and mental condition), social relationships (i.e., personal relationships, social support, and sex life) and environmental health (i.e., financial resources, safety, health and social services). It also contains QoL and general health items. The score ranges from 25 to 130 and is transformed linearly into a 0–100 scale.

The University of Rhode Island Change Assessment Scale (URICA) [71]: A self-report questionnaire consisting of 28 items rated on a 5-point Likert scale (from 1 = strongly disagree to 5 = strongly agree) representing four primary stages of change in Prochaska and DiClemente’s Trans-Theoretical Model (1982) [71], with 7 items for each of the following subscales: Precontemplation, Contemplation, Action, and Maintenance. To obtain a Readiness to Change total score, the items from each subscale must be summed, then divided by 7 to obtain the mean for each subscale. Following this, the means for the Contemplation, Action, and Maintenance subscales must be summed, and the Precontemplation mean subtracted (C + A + M − PC = Readiness).

Psychodiagnostic and psychological measures will be collected in group settings, in a dedicated room, by clinical psychologists independent of the study. Neuropsychological tests will be administered individually by neuropsychologists independent of the study in appropriate settings.

The duration of the assessment will be two hours for each patient, divided into two sessions (group and individual) on consecutive days.

Personal information will be entered and coded securely with quality control procedures (e.g., double data entry, range checks).

Data will be shared securely in compliance with data protection regulations to maintain participant confidentiality before, during, and after the trial.

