### 2.6. Procedure

Patients with AN will be invited to take part in the study at admission to the rehabilitation centers, according to the above-mentioned inclusion/exclusion criteria.

Before the randomization, they will be asked to sign the informed consent to participate in the study and to complete the psychodiagnostic (BAI, BDI II, OCI-R) measures.

Randomization will then be stratified by center and performed using the permuted block technique within each site by a researcher independent of the study. Participants will be assigned to one of two conditions: both groups will receive the usual hospital care (TAU), and the experimental group, in addition, will receive the CA-CRT treatment.

Before starting the program, all the participants will undergo neuropsychological testing (primary measures) and complete self-report psychological questionnaires (secondary measures).

The standard nutritional rehabilitation program is set up as a multidisciplinary treatment approach merging group therapies, individual therapies, and dietetic management in line with national guidelines [45]. Dietetic rehabilitation aims to encourage a change in eating habits and includes mealtime supervision, as well as both individual and group counseling provided by dietitians.

Individual sessions last from 30 to 45 min and encompass dietary assessment, evaluation of nutrient intake and adequacy, nutritional and anthropometric status, eating patterns, weight history, and patients’ readiness to change. Group meetings of around 20 people are provided every week and last about one hour. The main topics discussed include biological hunger, satiety, nutrients, weight management, and behavior change strategies for preventing relapse.

The patients’ meal plan is determined by the dietitian to gain half a kilogram (one pound) per week.

Meals last 60 min, followed by a 30 min mandatory resting period, where patients and staff members are together in a dedicated room. There are staff members present at all times during the meal and resting period.

Psychotherapy is provided once a week by a licensed psychotherapist in an individual setting and lasts about 45 min. Further, 1 h psychoeducational groups led by educationalists, psychologists–psychotherapists, or psychiatrists and focused on the relationship between food and emotions are provided weekly.

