Bodily experience is also specifically targeted through body image therapy (provided twice a week for 30 min by physiotherapists) and group dance therapy (provided once weekly by a psychologist and lasting 1 h) to help patients cope with a distorted body image.

Lastly, low-intensity physical activity based on gentle gymnastic sessions (3 times per week, 30 min per session) is provided to treat and normalize patients’ views and attitudes toward physical activity. Tailored activities in both individual and group settings are planned upon physical and functional assessment by professional physiotherapists.

The CA-CRT treatment will entail cognitive exercises aimed at improving more adaptive thinking styles, encouraging patients’ reflection on their way of elaborating information, and exploring the possibility of implementing new schemas in everyday life. The CA-CRT program will employ a wide range of cognitive tasks to address cognitive inflexibility and weak central coherence using the Italian translation of the CRT original manual [72]. The combined treatment will consist of 10 individual 40 min CA-CRT sessions, 2 times a week for 5 weeks, plus 15 individual CA-CRT 30 min sessions, 3 times a week for 5 weeks.

The description of the CA-CRT exercises for each session is reported in Table 1. The CA-CRT will consist of executive functions tasks, i.e., “sequence of symbols” and “answers by category”, as well as visual–perceptual processing, i.e., “figure memory”, and “geometric figure grids” retrieved from the Erica^®^ software (Giunti O.S., Florence, Italy). 

The total duration of the research will be 6 months, considering a discontinuous enrollment related to the patients’ admission to the clinics.

At the end of the treatment (after 5 weeks), recruited participants in both conditions will be administered the neuropsychological tests and the psychological questionnaires again.

Adherence will be supported through participant education and monitored via scheduled assessments and treatment logs.

As the study will be conducted in an inpatient unit with close clinical supervision, a formal monitoring plan is not required.

The experiential treatment can be discontinued in response to adverse events, participant request, or clinical changes. Participants will receive appropriate medical care for any trial-related harm.

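### A 5-week intervention with a post-test after 5 weeks does not fit inside the stated 1-month admission, and the article does not reconcile the two

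*Protocol article*

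**What the plan says.** All references are to the protocol article.

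- **Admission and recruitment (section 2.2):** "Participants will be recruited in the first week of admission to the 1-month nutritional rehabilitation program in the three specialized centers".
- **Assignment (section 2.4):** "Participants will be assigned to one of two conditions within the first week from the baseline assessment".
- **Baseline testing (section 2.6):** "Before starting the program, all the participants will undergo neuropsychological testing (primary measures"). Section 2.5 describes each assessment as "divided into two sessions (group and individual) on consecutive days".
- **Intervention (section 2.6):** "10 individual 40 min CA-CRT sessions, 2 times a week for 5 weeks", together with "15 individual CA-CRT 30 min sessions, 3 times a week for 5 weeks".
- **Post-test (section 2.6):** "At the end of the treatment (after 5 weeks), recruited participants in both conditions will be administered the neuropsychological tests".

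The Introduction frames the hypothesis over a 5-week intervention period, and section 2.3 gives the same pre-post interval for the sample size. Section 2.6 describes the study as run in an inpatient unit. Section 3 confirms a pre-post design without further follow-up. No visible section mentions an extended stay, sessions after discharge, usual care after discharge, or a return visit for testing.

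**The concern.** The rehabilitation program is given as one month. The intervention, which starts only after admission, recruitment, baseline testing and assignment, is given as five weeks, with the post-test at its end. The two figures cannot both hold for a patient whose stay is the stated month.

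The timing matters because the post-test is the only post-baseline measurement, so every primary and secondary outcome depends on it. Usual care here is an inpatient package of supervised meals, therapy and activity. Its amount therefore depends on how long a patient stays. Participants and therapists know the allocation (section 2.4). If sites had to improvise at the end of the month, length of stay or test date could come to depend on arm, and part of a between-arm difference would then reflect extra usual care or a different test-retest interval. The Introduction also lists retention among the feasibility indices, and a schedule longer than the program can lower retention for reasons unrelated to how acceptable the intervention is.

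**Working it through.** **Inputs from the article**
- Session series: 10 sessions at 2 per week; 15 sessions at 3 per week (section 2.6).
- Recruitment: days 0 to 7 of admission (section 2.2).
- Assignment: up to 7 days from baseline (section 2.4).
- Program length: 1 month (section 2.2).

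**Assumptions**
- The article gives no number of days for the month, so I take 28, 30 and 31.
- It gives no separate interval between assignment and first session, so I take zero.

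**Step 1. Reproduce the stated duration.** Sessions divided by sessions per week: 10/2 = 5 weeks and 15/3 = 5 weeks. 5 × 7 = 35 days. The two series agree with each other and with the 5-week post-test.

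**Step 2. Overrun.** Let L be the days from admission to treatment start and M the length of the month. The post-test is due on day L + 35, so the overrun is L + 35 − M.

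| Lag L | Post-test day | Overrun, M = 28 | M = 30 | M = 31 |
|---|---|---|---|---|
| 0 | 35 | 7 | 5 | 4 |
| 7 | 42 | 14 | 12 | 11 |
| 14 | 49 | 21 | 19 | 18 |

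L = 0 is the most favourable case and is not attainable in practice, because baseline testing takes two consecutive days and comes before the program. With L = 2 the post-test falls on day 37, an overrun of 6 to 9 days. L = 14 is 7 + 7: recruitment and baseline at the end of week one, then the full assignment window.

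**Step 3. Sessions that fit in the month.** The plan has 2 + 3 = 5 sessions a week, 25 in all. Those that fit number 5 × (M − L)/7:

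| Lag L | M = 28 | M = 30 | M = 31 |
|---|---|---|---|
| 0 | 20.0 | 21.4 | 22.1 |
| 7 | 15.0 | 16.4 | 17.1 |
| 14 | 10.0 | 11.4 | 12.1 |

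**Step 4. Most lenient reading.** If sessions run Monday to Friday and the first is on day 1 of admission, the last falls on day 4 × 7 + 5 = 33. That is still past a 31-day month, before any post-test.

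No month length and no start date within the stated windows removes the overrun.

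**The case against.** The strongest reply is that one month is a loose label for the program and not a maximum stay. The article gives no discharge date, calls the study inpatient, and may simply intend participants to stay for the full five weeks. That reply is fair, and it limits what may be concluded. The mismatch between the two durations remains, because no visible text provides for the longer stay. The flowchart (Figure 1) and the supplementary checklist are not available here and might say more.

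A reader might infer four stronger things that the article does not support.

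- **That sessions and tests will fall after discharge.** This follows only if discharge comes at the end of the stated month.
- **That the control arm's test time is left open.** It is not. Section 2.6 re-tests both conditions after 5 weeks, and section 2.3 gives one interval for all recruits. Only the day from which the 5 weeks are counted is loose.
- **That the arms will be handled differently.** Nothing says so. Both arms receive usual care and have the same stated test time, and the calendar mismatch itself affects both. Differential handling is a risk under open allocation, not a stated fact.
- **That the shortfall is about three weeks.** The 18 to 21 days, with 10 to 12 sessions fitting, need late recruitment, a full and non-overlapping assignment window, and discharge at one month. Section 2.6 invites patients at admission, and the two windows are upper limits that may overlap.

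How discharge is handled day to day is detail that an article may leave to the full protocol. Two stated durations that disagree are not of that kind.

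**Conclusion.** The contradiction holds as written. The firm part is the minimum: 35 days against 28 to 31, an overrun of 4 to 7 days with no lag at all. A 7-day lag makes it 11 to 14 days, and the worst case of the stated windows 18 to 21 days. These figures rest on a month of 28 to 31 days and on the session rates in section 2.6.

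The consequences are conditional. If patients leave at the end of the month, part of the intervention and the only post-baseline assessment would fall after discharge. Arm-dependent stays or test dates, and retention lost to the calendar, then become possible. Since the conflict touches the sole outcome time point in both arms and is cheap to remove, it should be settled before enrollment goes further.

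**What to change.** 1. Reconcile the admission length (section 2.2), the recruitment and assignment windows (sections 2.2 and 2.4), and the intervention and assessment schedule (section 2.6). Which schedule applies is for the clinical team to decide.
2. Keep the common 5-week post-test already stated for both arms, but count it from randomization. Controls have no CA-CRT start date, so randomization is the origin that both arms share. Any interval between randomization and first session should be settled under item 1, so that the test date and the end of treatment agree.
3. State that the post-test is carried out at that time in both arms regardless of discharge or number of sessions attended.

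The cost is a protocol amendment and possibly return visits for some participants who have already left. Sample size and choice of outcomes are not affected.

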### 2.3. Sample Size Calculation

The minimum sample size required for this study has been computed using an *a priori* sample size calculator (G*Power 3.1.9.2 software) for the *F* tests [46,47,48]. Participants will be randomly allocated into two groups: (A) TAU plus CA-CRT condition (experimental group) and (B) TAU-only condition (control group). Moreover, the recruits will be assessed before and after the intervention (i.e., 5 weeks). The Pillai V has been set *a priori* to take a value of 0.2, with an effect size of 0.5. Moreover, the type I error (*α*) rate has been set at 0.05 (two-sided), and the power (1 − *β*) at 0.95, respectively. The results showed that there is a 95% chance of correctly rejecting the null hypothesis of no significant interaction effect, with 54 recruits in total (27 per group) for each center.

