## Abstract

**Background/Objectives:** Anorexia nervosa (AN) is marked by cognitive deficits, particularly reduced mental flexibility and weak central coherence, which may sustain the core psychopathological symptoms. While cognitive remediation therapy (CRT) has shown efficacy in improving these cognitive processes in AN, evidence on computer-based CRT remains limited. This study aims to evaluate the feasibility and efficacy of integrating computer-assisted cognitive remediation therapy (CA-CRT) into standard nutritional rehabilitation (treatment as usual, TAU) to improve the targeted cognitive and psychological parameters among inpatients with AN in a more personalized and scalable way. **Methods**: A multicenter randomized controlled trial (RCT) will be conducted. At least 54 participants with a diagnosis of AN will be recruited at each site and randomized into either the experimental or control group after initial screening. The intervention will last five weeks and include 15 individual CA-CRT sessions alongside 10 individual CR sessions, delivered in addition to standard care. The primary and secondary outcomes will be assessed at the end of the intervention to evaluate the changes in cognitive flexibility, central coherence, and psychological functioning. **Results**: Participants receiving CA-CRT are expected to develop more flexible and integrated thinking styles and achieve greater improvements in clinical outcomes compared to those receiving standard care alone, supporting a more personalized therapeutic approach. **Conclusions**: These findings would underscore the feasibility and clinical value of incorporating CA-CRT into standard inpatient treatment for AN. By specifically targeting cognitive inflexibility and poor central coherence in a scalable, individualized format, CA-CRT may enhance treatment effectiveness and support the development of patient-centered interventions tailored to the cognitive profiles of individuals with AN.

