Despite these available options, recent systematic reviews and meta-analyses consistently reported discouraging outcomes, with non-response rates ranging from 30% to 50%, high treatment dropout, and frequent relapse following weight restoration. For example, Berends et al. (2018) reported relapse rates of approximately 31% within 1–2 years [10], while Frostad et al. (2022) found that nearly half of patients relapsed within 12 months post-discharge [11]. A 2024 meta-analysis by de Rijk et al. confirmed a mean relapse rate of 37% over an average follow-up of 31 months, identifying a lower post-treatment BMI and higher baseline depression as significant predictors of relapse [12]. Similarly, a rapid review by Miskovic-Wheatley et al. (2023) reported relapse rates ranging from 41% at the 1-year follow-up to 30% at 22 years [13]. These findings underscore the urgent need for novel, adjunctive treatment strategies that address not only the core maintaining mechanisms of AN—such as weight restoration and disordered eating behaviors—but also broader domains essential for sustained recovery. These include improvements in psychological well-being, interpersonal functioning, emotional regulation, identity development, and overall quality of life, which are often profoundly affected by the disorder. Interventions targeting these broader outcomes should be designed to complement existing treatment frameworks and be feasibly integrated into established care pathways [14,15].

In particular, the consistent findings in the literature highlight two core neurocognitive difficulties commonly associated with AN: cognitive inflexibility—primarily manifested as weak set-shifting abilities [16]—and extreme attention to detail, often described as weak central coherence [17,18,19]. Cognitive flexibility refers to the ability to adjust and respond to evolving environmental requirements by flexibly switching between different rules, tasks, actions, and mental frameworks [20]. Consequently, impaired set-shifting or cognitive inflexibility leads to rigid or persistent thinking and behavior. Central coherence pertains to the ability to process information globally or holistically, whereas weak central coherence is reflected by an excessive focus on detail [21].

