Therefore, the present multicenter randomized controlled trial (RCT) aims to implement and evaluate a personalized CA-CRT program for individuals with AN as an adjunct to standard nutritional rehabilitation (treatment as usual, TAU). The study will test the feasibility and efficacy of CA-CRT in enhancing selected neuropsychological outcomes (cognitive flexibility and central coherence) and psychological measures (eating disorder symptomatology, health-related quality of life, and motivation to change) among inpatients with AN. The feasibility of the study will be evaluated through indices such as the recruitment and retention rates and the patient outcomes. These metrics will help determine not only whether the intervention is acceptable but also whether it can be implemented in routine clinical settings. By delivering a structured, scalable, and individually tailored intervention, the trial seeks to promote more effective, patient-centered care approaches. It is hypothesized that participants allocated to the experimental group will demonstrate greater improvements in the targeted outcomes compared to those receiving standard care alone over the 5-week intervention period. Specifically, the primary hypothesis is that participants in the CA-CRT group will show significantly greater improvement from baseline to post-treatment than those in the TAU group in relation to cognitive flexibility, as measured by the Wisconsin Card Sorting Test (WCST), the Phonemic/Semantic Alternate Fluency Test, the Trail Making Test (TMT), the Test of Attentional Performance (TAP), the Detail and Flexibility Questionnaire (DFlex), and the Cognitive Flexibility Inventory (CFI). Improvements are also expected in the Central Coherence Index (CCI) of the Rey–Osterrieth Complex Figure (ROCF-C).

The secondary hypothesis is that the CA-CRT group will show greater reductions in their eating disorder symptoms (EDE-Q), as well as greater improvements in their quality of life (WHOQOL-BREF) and readiness to change (URICA), compared to those receiving TAU.

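### Section 2.3 attaches 95% per-centre power to 54 recruits, but 54 is the exact minimum with both assessments, so the figure leaves nothing for loss

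*Protocol article*

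**What the plan says.** The sample-size section (2.3) describes a G*Power calculation for F tests, with two groups assessed before and after the five-week intervention. Pillai V is set "to take a value of 0.2, with an effect size of 0.5", alpha at 0.05 two-sided and power at 0.95. The result is stated as follows: "there is a 95% chance of correctly rejecting the null hypothesis of no significant interaction effect, with 54 recruits in total (27 per group) for" every centre. The Abstract uses the same number as a recruitment floor: "At least 54 participants with a diagnosis of AN will be recruited at each site". Neither place mentions an allowance for loss.

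Elsewhere the article treats retention as uncertain. The Introduction reports, for AN treatment in general, "non-response rates ranging from 30% to 50%, high treatment dropout, and frequent relapse following weight restoration". It also says: "The feasibility of the study will be evaluated through indices such as the recruitment and retention rates and the patient outcomes". Section 2.6 says that the experimental treatment "can be discontinued in response to adverse events, participant request, or clinical changes". Section 2.7 says that missing data will be dealt with by suitable methods, without naming one. No expected dropout rate for this trial is given.

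**The concern.** A power calculation of this kind returns the number of participants who contribute to the test. The group-by-time interaction compares pre-post change between arms, so a participant contributes fully only with both assessments. Section 2.3 takes the calculated number and prints the power against recruits. If 54 is exactly what the calculation needs, each participant lost in a centre takes that centre below the stated 95%.

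What is at stake is how a null result would be read. Someone looking at one centre's result against a claimed type II error of 5% would be using a figure that applies only with complete follow-up.

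**Working it through.** **Inputs, all from section 2.3 unless noted.** V = 0.2; effect size 0.5; alpha = 0.05; target power 0.95; 2 groups; 2 measurements; 54 per centre. Three centres (section 2), so 3 × 54 = 162 recruits if pooled. Dropout rate: not stated, so a range is assumed.

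**Step 1: are the two effect-size figures consistent?** With two groups and two measurements, s = min(2 − 1, 2 − 1) = 1, and f(V) = √(V/(s − V)) = √(0.2/0.8) = 0.5. They agree, and f² = 0.25.

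**Step 2: reproduce the plan's figure.** The G*Power convention for the within-between interaction uses a noncentral F with df1 = 1, df2 = N − 2 and λ = N × f² = 0.25N.

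- N = 54: λ = 13.5, df2 = 52, power 0.9501.
- N = 53: λ = 13.25, df2 = 51, power 0.9464.

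The smallest N reaching 0.95 is 54, so the printed figure is reproduced exactly and contains no reserve. (With λ = (N − 2) × f², power at 54 would be 0.9427 and 56 would be needed. The plan's figure matches the first convention, which is used below.)

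**Step 3: 54 recruited in a centre, completers only analysed.** Completers = 54 × (1 − loss), rounded to the nearest whole number.

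| Assumed loss | Completers | λ | df2 | Power |
|---|---|---|---|---|
| 0% | 54 | 13.5 | 52 | 95.0% |
| 10% | 48.6 → 49 | 12.25 | 47 | 92.9% |
| 20% | 43.2 → 43 | 10.75 | 41 | 89.3% |
| 30% | 37.8 → 38 | 9.5 | 36 | 85.1% |

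Rounding down gives 92.4% (48) at 10% and 84.1% (37) at 30%. At 44 completers (10 of 54 lost, 18.5%) power is 90.0%, so the type II error has doubled from 5% to 10%.

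**Step 4: the same effect with the three centres pooled.**

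- No loss: N = 162, λ = 40.5, power above 99.99%.
- 30% loss: 162 × 0.7 = 113.4 → 113, λ = 28.25, power 0.9995.
- At least 54 completers remain until two thirds are lost (1 − 54/162 = 0.667).

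**The case against.** The strongest reply is that nothing is miscalculated. A reader might infer from Step 3 that the stated power is wrong. It is not: 54 at 95% follows exactly from the printed inputs. What does not fit is attaching the figure to recruits. This part of the reply stands.

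A second reply is that the trial is one multicentre study. Section 2.7 describes a single MANCOVA and no separate centre analyses, although it does not say explicitly that centres are pooled. In a pooled analysis, dropout is no threat to 95% power for this effect. This also stands, and it limits the point to the per-centre claim. A reader might still infer that the trial is underpowered. The documents do not support that: even in a single centre, 34 completers give 80% power, so up to 20 of 54 (37%) could be lost before power fell below that level. Nor can a pooled shortfall be argued from the number of outcomes. The article gives no count of jointly tested scores for such a calculation, and that would be a different issue from loss.

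Third, 54 is a minimum, and the Abstract's wording allows more to be recruited. That is true, but no rule for replacing losses is given, and section 2.3 still prints the power against 54 recruits.

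Fourth, a reader might infer that the article forecasts dropout in this trial. It does not. The dropout remark in the Introduction summarises AN treatment generally, a retention index is not a prediction, and a patient who stops the experimental sessions can still be assessed at five weeks. What stands is narrower: the article does not treat complete retention as given. Missing-data methods may also recover part of the loss, but none is named, so full recovery cannot be assumed.

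Finally, a condensed article may leave the dropout allowance to the full protocol. The point does not rest on that omission. It rests on a stated power printed against a count to which it applies only with no loss.

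**Conclusion.** The point holds, and it is minor. On the printed inputs, 54 is the bare minimum with both assessments, so 95% per-centre power for 54 recruits requires zero loss. The shortfall is about 2 points at 10% loss, 6 at 20% and 10 at 30%. These sizes assume one outcome at V = 0.2, analysis of completers only, exactly 54 recruited per centre, and loss rates that are not in the article. For the three centres pooled, on the same single-outcome effect, the shortfall has no practical consequence.

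**What to change.** Reword section 2.3 in four respects:

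1. Define 54 (27 per group) as the number of participants with both the baseline and the post-treatment assessment.
2. State the dropout that is assumed.
3. Restate the power for 54 recruited per centre at that dropout; the table above gives the values on the present inputs.
4. Say whether the stated power refers to each centre or to the pooled sample.

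The cost is a few sentences and a somewhat less favourable per-centre figure. No added enrolment is needed. If the sponsor prefers to keep 95% for each centre, the Abstract's floor wording already leaves room to define the target as 54 completers per centre. That would mean 54/(1 − loss) recruits: 60 at 10%, 68 at 20% and 78 at 30%, rounded up to equal arms. The pooled result gives no reason to require this.
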